### Concealment mechanism {16b}

Only 30 of the eligible schools will join the trial based on our pre-estimated sample size. The initial selection of 30 schools will use www.random.org. All of the schools’ names will receive a number from one to the total number of eligible schools (i.e., if there are 42 eligible school names, then each one will receive a number from 1 to 42). A random number generator will select 30 numbers from a range of 1 to the total number of eligible schools. These 30 numbers will be randomly assigned to control or intervention groups using Efron’s biased coin to ensure balanced groups. All schools recruited in the same city will be randomized simultaneously. Randomization within each city will be performed when all schools are recruited for that city, rather than waiting until all schools (across all cities) are recruited and then performing randomization of all schools simultaneously. Members of the trial team who are involved with recruitment of schools will be unaware of previous allocations. Trial researchers, not involved with school recruitment, will inform schools of their randomized allocation.

### Implementation {16c}

All schools from the 30-school lists that give consent for participation and fulfil the inclusion criteria will be randomized. The staff member responsible for the recruitment and baseline interviews will request the randomization. The Ministry of Health team will implement all stages of the intervention, including the recruitment, informing of intervention treatment and supervision.

## Assignment of interventions: blinding

### Who will be blinded {17a}

Due to the nature of the intervention, neither teacher participants nor school staff can be blinded to the allocation. Data collection team will be blind to which group (control or intervention) the school will be allocated. We will not directly provide information on the school allocation to the external assessors who will interview the teachers, but no one is truly blinded in this type of randomized controlled trial because the teachers may accidentally report the school status.

### Procedure for unblinding if needed {17b}

Not applicable. This trial does not have the potential to harm or other relevant conditions that necessitate an unblinding protocol prevention.

## Data collection and management

### Plans for assessment and collection of outcomes {18a}

The main outcome of the study is the behavioural repertoire of the children, including problem behaviours, such as disruptiveness, aggressiveness and shyness, and prosocial behaviours. We will control for covariates, such as the gender and age of teachers and children, and the teachers’ stress levels and senses of self-efficacy. The main outcome will be collected using the TOCA-C, which is an instrument to measure the social adaptation behaviours of elementary school students. The teacher answers the 21 items of the instrument and classifies the frequency of each student’s behaviours in the classroom on a Likert scale (ranging from “never” to “almost always”). The TOCA-C was designed to investigate disruptive behaviours or problems with concentration and social skills [42]. The instrument was translated by the team of researchers responsible for the project, who will also perform validation and cultural adaptation to Brazil. Covariates will be collected using the Student-Teacher Relationship Scale-Short Form (STRS-SF), which is a sociodemographic questionnaire on age, gender, education and length of professional experience. Teacher socioeconomic status will be collected using the Index of the Brazilian Association of Research Companies. Sense of competence will be assessed using the Bäbler and Schwarzer General Self-Efficacy Scale as adapted by Gil-Monte and Moreno-Jiménez. Teachers’ mental health will be assessed using the Self-reporting Questionnaire (SRQ 20).

### Plans to promote participant retention and complete follow-up {18b}

A study supervisor and trained supervisor will provide periodic communication via weekly meetings and presentations to inform the school officials/staff, students and parents about the Elos 2.0 Programme, the current status of the programme and plans for the next phase. These supervisors will also acknowledge their support in periodic meetings and motivational posts on social media.

### Data management {19}

In the Elos 2.0 Programme, all data from the Elos 2.0 Programme will be entered in two stages: (1) interviewers will enter documents in the proper form and (2) all of the data will be entered electronically. These entries may be done at the participating site where the data was originated. Original study forms will be entered and kept on file at the participating site. A subset will be requested later for quality control. When a form is selected for review, the participating site staff will pull that form, copy it and send the copy to the study supervisor for re-entry. Participant files will be stored in numerical order in a secure and accessible place and manner. All forms related to study data will be kept in locked cabinets and access to the study data will be restricted to the study supervisor and assigned data management member staff. Participant files will be maintained in storage for three years after completion of the study. Errors will be detected by the study supervisor and data management member staff who are assigned to detect missing data or specific errors in the data.

### Confidentiality {27}

All study-related information will be stored securely at the study site. All participant information will be stored in locked file cabinets in areas with limited access. All data collection, processes and administrative forms will be identified using a coded ID [identification] number only to maintain participant confidentiality. All records that contain names or other personal identifiers, such as locator forms and informed consent forms, will be stored separately from the study records identified by the code number. Forms, lists, logbooks, appointment books and any other listings that link participant ID numbers to other identifying information will be stored in a separate, locked file in an area with limited access.

### Plans for the collection, laboratory evaluation and storage of biological specimens for genetic or molecular analysis in this trial/future use {33}

Not applicable. No biological specimens will be collected as part of this trial.

## Statistical methods

### Statistical methods for main outcomes {20a}

Four two-level regression analyses for the observed continuous dependent measures will be performed (one analysis for each subscale of the TOCA and one for TOCA general score; disruptiveness, concentration problem and prosocial behaviour). Each grade has a teacher who is responsible for the implementation of the Elos 2.0, and consequently, teacher and classroom effects are not dissociable. There is no cross-classification between teachers and classrooms (i.e., a teacher for the first grade will be solely responsible to this group of students). Moreover, all the classroom within the same school receives the same intervention (i.e., Elos 2.0 or treatment as usual).

This multilevel analysis will be dealt on Mplus version 8.4 under the maximum likelihood with robust standard errors (MLR). This estimator allows dealing with the non-independence of the observation (i.e., children nested classrooms); the standard error will be computed considering such multilevel structure by command in Mplus called (TYPE = Complex) using a sandwich estimator where the cluster variable will the classroom (i.e., teachers level) [43]. Adopted statistical significance was 0.05. Important to note that although within the school with have different classroom, all the classrooms within the same school are receiving either Elos 2.0 or treatment as usual to avoid contamination among the teachers. Therefore, our analysis will be following a two-level approach. In case of moderate or strong differences or unbalanced proportions between the control/intervention schools and/or children features on baseline measurements, the later will be inserted as covariates in the model for estimating the intervention effects. The only exception will be the baseline values of the outcome variables, which will be included in the within part as a predictor of the targeted outcome. This approach is also called the residualized change score [44].

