## Objectives {7}

The main objective of this cluster-randomized controlled trial is to evaluate the effectiveness of the Elos 2.0 Programme, which is a version adapted to Brazil for proposed implementation by the Ministry of Health, in the reduction of problem behaviours and promotion of prosocial behaviours in children in public schools. All outcomes are measured at the level of the individual child. Our main hypothesis is that students between the first and fourth years of elementary school who are exposed to the Elos 2.0 programme for 5 months will have a lower frequency of problem behaviours (e.g., disruptiveness, aggressivity and shyness) and better prosocial behaviours compared to the control group.

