### Outcomes {12}

Main outcome is as follows: child problems and prosocial behaviours. All outcomes will be measured at the individual level, but analyses will be multilevel based on schools and individuals. The main outcome is a variable compound of three measures (child concentration, disruptive problem and prosocial behaviour) that are measured using only one instrument, the Teacher Observation of Classroom Adaptation-Checklist (TOCA-C). The main outcome measure is completed twice for each child by teachers with mediation of a trained interviewer: at baseline (before trial is implemented) and after trial completion.

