### Sample size {14}

Our target between group mean difference for TOCA scores was 0.25, which we believe to be a plausible treatment effect for this intervention, and would be clinically meaningful. A sample size of *N* = 3000 child participants (1500 in each treatment group), comprising 15 clusters with an average of 100 children per cluster, is sufficient to provide 92% power, with an alpha threshold of 0.05, a standard deviation of 0.80 based on the study by Storr et al. [40], an intraclass correlation coefficient of 0.05 (a conservative value compared with a previously reported value of 0.039 by Liljequist et al. [41]), and setting the coefficient of variation of cluster sizes at 0.70.

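### One compound main outcome is defined and one difference is powered, but four main-outcome regressions are planned at 0.05 without saying which one decides the trial

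*Protocol article*

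**What the plan says.** Four places in the protocol article bear on which result decides the trial.

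- **Outcomes {12}** describes a single main outcome: "The main outcome is a variable compound of three measures (child concentration, disruptive problem and prosocial behaviour"), all taken from the TOCA-C.
- **Sample size {14}** is built on one contrast: "Our target between group mean difference for TOCA scores was 0.25", "with an alpha threshold of 0.05, a standard deviation of 0.80". It does not say whether this is a subscale or the general score.
- **Statistical methods for main outcomes {20a}** plans four analyses: "Four two-level regression analyses for the observed continuous dependent measures will be performed", namely "one analysis for each subscale of the TOCA and one for TOCA general score". The level is given once: "Adopted statistical significance was 0.05". None of the four is ranked first.
- **Objectives {7}** states the main hypothesis over several behaviours: exposed children "will have a lower frequency of problem behaviours (e.g., disruptiveness, aggressivity and shyness) and better prosocial behaviours compared to the control group".

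The missing-data section {20c} does use the term primary analysis, but there it selects the analysis set (intention to treat, observed data only). It does not select one of the four scores.

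**The concern.** One main outcome in one section becomes four main-outcome analyses in another, and the power statement is attached to none of them by name. The article never says that the general score is the compound variable of the Outcomes section, so the reader cannot tell which p-value settles the main hypothesis.

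This matters most if results are mixed, for example a significant gain in prosocial behaviour with no difference in disruptiveness. The text as it stands could then be read as supporting either success or failure, and the choice could be made after the results are seen. The stated 0.05 and 92% belong to one test; whether they describe the trial depends on a rule that the article does not give.

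**Working it through.** **1. The plan's own power figure.** Inputs from Sample size {14}: difference 0.25, SD 0.80, ICC 0.05, 15 clusters per arm, mean cluster size m = 100, coefficient of variation of cluster size 0.70. Sidedness is not stated.

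- λ = m·ICC / (m·ICC + 1 − ICC) = 5 / 5.95 = 0.840
- Design effect = [1 + (m − 1)·ICC] / [1 − CV²·λ(1 − λ)] = 5.95 / (1 − 0.49 × 0.134) = 6.37
- Effective n per arm = 1500 / 6.37 = 235.5
- SE = 0.80 × √(2 / 235.5) = 0.0737, so the expected z = 0.25 / 0.0737 = 3.39
- Two-sided power at 0.05 = Φ(3.39 − 1.96) = 92.4%

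This reproduces the stated 92% for **one** test. With a t distribution on 28 df it is 90.5%. A one-sided 0.05 test with the same design effect would give 96.0%, so a two-sided test is taken as intended.

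**2. Decision rule: any one of the four.** The article gives no correlation between subscales, so a range is shown. Assumptions: three null test statistics with common correlation r, a general score equal to their sum, otherwise valid standard errors, and each test two-sided at 0.05. The quantity is P(at least one |z| > 1.96 among the four), by simulation with 2,000,000 draws per value of r. The benefit-only column counts only z > 1.96, with all scores oriented so that higher is better.

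| Assumed r | Any false significant difference, either direction | False difference in the benefit direction |
|---|---|---|
| 0 | 16.1% | 8.2% |
| 0.3 | 14.4% | 7.2% |
| 0.5 | 13.0% | 6.5% |
| 0.7 | 11.1% | 5.5% |
| 0.8 | 9.9% | 4.9% |
| 0.9 | 8.4% | 4.2% |
| One test | 5% | 2.5% |

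Weighting the subscales unequally (9:7:5) in the general score changed these figures by less than 0.1 percentage point. The independence formula, 1 − 0.95⁴ = 18.5%, does not apply, because the general score is taken to be a function of the subscales.

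**3. Decision rule: all three subscales.** A claim that needs every test to be significant has type I error no larger than that of a single test, so it stays at or below 5%. Power changes. If each subscale had 92% power (mean shift 1.96 + 1.405 = 3.365), the chance that all three are significant is 80% (r = 0.3), 82% (0.5), 84% (0.7) or 86% (0.8).

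**4. Decision rule: general score alone.** The error rate is 5%. Power is 92% if the 0.25 difference and the 0.80 SD describe that score, which the article does not say.

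**5. Cost of keeping several co-primary tests.** Bonferroni over four (0.0125 each): Φ(3.39 − 2.50) = 81.4% for one score at the stated inputs. Over three subscales (0.0167 each): 84.1%.

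**The case against.** The strongest reply is that a primary outcome has in effect been named. The Outcomes section gives one compound variable, the sample size gives one difference, and the analysis includes a general score. Read together, the general score is the compound, the subscale regressions describe its components, and the 5% stands. This is the reading closest to the Outcomes section, and nothing in the article contradicts it. But the article does not state it either: the general score is listed beside the subscales under the same heading and the same level.

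A second reply is that multiplicity procedures are commonly left to an analysis plan, which is not shown here. That is fair, and the lack of an adjustment is not the point. The point is that stated sections disagree on whether there is one main-outcome test or four.

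Two stronger readings are tempting and should be resisted.

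- A reader might infer that the trial carries a 10-14% chance of a false claim of **benefit**. That range counts significant differences in either direction. With the two-sided tests that the 92% power implies, the benefit-only figure is about half as large.
- A reader might infer that the error rate **is** inflated. It is inflated only if any one of the four suffices, a rule that the article neither states nor excludes. The main hypothesis joins fewer problem behaviours with "better prosocial behaviours compared to the control group", and that conjunction points away from such a rule.

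**Conclusion.** The concern holds as a conflict about which test decides the trial, not as a demonstrated inflation of error. Three decision rules fit the text:

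- **Any of four:** roughly two to three times the nominal error. The chance of a false significant difference in either direction is about 10-14% for r of 0.3-0.8 (8-16% for r of 0-0.9), against 5%; in the benefit direction it is about 5-7% for r of 0.3-0.8, against 2.5%.
- **All three subscales:** error at or below 5%, joint power about 80-86% rather than 92%, assuming that each subscale has 92%.
- **General score alone:** 5% holds, and 92% holds if the sample-size difference and SD belong to that score.

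The subscale correlations, the general score as a sum of the subscales and the 92% power per subscale are assumptions; the article gives none of them. The ambiguity itself rests on the quoted text alone.

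**What to change.** - In Outcomes {12} and Statistical methods for main outcomes {20a}, name the TOCA general score, with its scoring direction, as the single primary outcome, tested at two-sided 0.05.
- In Sample size {14}, state which score the 0.25 difference and the 0.80 SD refer to. If it is not the general score, restate the power for the general score.
- Make the three subscales secondary with a stated multiplicity procedure, for example tested only if the primary is significant, with Holm across the three.

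The cost is wording, plus a recalculated power figure if the inputs belong to another score. The primary test keeps its full 0.05, and the subscale tests become slightly stricter. Keeping all four as co-primary with Bonferroni is also valid but dearer: power for one score at the stated inputs falls from 92.4% to 81.4%.

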## Trial design {8}

A cluster-randomized controlled superiority trial will be performed in 30 schools in three cities (15 controls and 15 in the experimental group), with a total of 3800 children participating in the test (1900 in the control group and 1900 in the intervention group). This study is a randomized controlled trial with two parallel groups (intervention and control) of students aged 6 to 10 years and enrolled in the first to fourth year of elementary education in public schools in the cities of Fortaleza, Eusébio and São Paulo, which are located in the states of Ceará and São Paulo. The ratio of intended numbers of participants in each of the comparison groups is 1:1. The control group receives treatment as usual in Brazil, i.e., no behavioural intervention at the school.

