## Assignment of interventions: allocation

### Sequence generation {16a}

The allocation of schools (1:1) to the control or intervention group will be performed via simple random drawing from the list of the Anísio Teixeira National Institute of Educational Studies and Research (INEP, its acronym in Portuguese), which includes all Brazilian schools separated by city. Randomization will be performed using a quantitative methodology in PASS 15 Efron’s biased coin (two treatments, equal sample sizes). The target sample sizes are the same for both groups. To achieve a longitudinal balance between groups, the algorithm dynamically changes the group assignment probabilities.

The unit of randomization between groups is the schools and not the classes. Therefore, there will be no control classes in an experimental school and vice versa to avoid sample contamination. Agreement to participate in the study was received from the schools before randomization.

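### With only 30 randomised schools, large-sample ML with an uncorrected sandwich standard error stays liberal even after the cluster is changed from classroom to school: about 6-9% at a nominal 5% if cities do not differ

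*Protocol article*

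**What the plan says.** The section on statistical methods for main outcomes {20a} plans two-level regressions for the three TOCA subscales and the general score. They are to be fitted in Mplus "under the maximum likelihood with robust standard errors (MLR"). Standard errors come from the TYPE = Complex option, "using a sandwich estimator where the cluster variable will the classroom", and the significance level is 0.05. No degrees of freedom, reference distribution or small-sample correction is given.

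The independent units are few. Trial design {8} gives "30 schools in three cities (15 controls and 15 in the experimental group"), and Sequence generation {16a} says "The unit of randomization between groups is the schools and not the classes". Outcomes {12} describes a school-level structure: "analyses will be multilevel based on schools and individuals". Sample size {14} expects very unequal schools, "setting the coefficient of variation of cluster sizes at 0.70". The comparators section {6b} and Concealment mechanism {16b} place the 1:1 allocation within each city; {20a} does not list city as a model term.

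**The concern.** The arm effect is a contrast between 15 schools and 15 schools, so about 28 degrees of freedom inform its variance. An uncorrected sandwich is biased downward with so few clusters, more so when sizes are unequal. ML without the REML adjustment also underestimates the between-school variance. A normal critical value then ignores that this variance is estimated from 30 schools.

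The obvious repair to {20a} is to put school in place of classroom in the same command, as {12} suggests. That takes the analysis from at least 120 classrooms (30 schools with at least one class in each of four grades) to 30 clusters, where the large-sample argument is weakest. At stake are confidence intervals that are too narrow and a result just under 0.05 that a correctly sized test would not call significant.

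**Working it through.** **Inputs.** From Trial design {8}: 15 schools per arm. From Sample size {14}: mean 100 children per school, CV of school size 0.70, ICC 0.05 (0.039 previously reported), SD 0.80, difference 0.25, power 92%. From {20a}: level 0.05. Assumed: two-sided test, normal reference, gamma-distributed school sizes.

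**1. The plan's power figure.**
- L = m·ICC / (m·ICC + 1 − ICC) = 5 / 5.95 = 0.840
- Relative efficiency RE = 1 − CV²·L·(1 − L) = 1 − 0.49 × 0.840 × 0.160 = 0.934
- Design effect = [1 + 99 × 0.05] / RE = 5.95 / 0.934 = 6.37
- Effective n per arm = 1500 / 6.37 = 235.5
- SE = 0.80 × √(2 / 235.5) = 0.0737, and 0.25 / 0.0737 = 3.39
- Power = 92.4% with a normal reference, so the stated 92% reproduces. With t on 28 df it is 90.5%.

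**2. Closed form for equal schools, school as cluster.** The sandwich variance is the sum over arms of Σ(h·e)², where h is the school's share of its arm and e is its deviation from the arm mean.
- With h = 1/15 its expectation is 14/15 = 0.933 of the true variance.
- Comparing with 1.96 is therefore the same as comparing a t(28) statistic with 1.96 × √0.933 = 1.894, which has two-sided probability 6.9%.
- With the factor C/(C − 1) = 30/29, the critical value is 1.926 and the rate 6.4%.
- The normal reference alone, with an unbiased variance, gives 6.0%.

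**3. Simulation under no effect, school as cluster, reference 1.96, no city effect.** Each setting had 10,000 or 20,000 trials (Monte Carlo standard error about 0.15 to 0.22 percentage points).

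| Method | Equal schools | CV 0.70 |
|---|---|---|
| Pooled sandwich, no factor | 6.3-6.8% | 8.5-9.0% |
| Pooled sandwich, C/(C − 1) | 6.2-6.4% | 8.0-8.5% |
| Fitted two-level ML, robust SE (ICC 0.05) | 6.3% | 6.8% |

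The sandwich rows cover ICC 0.02 to 0.05. A child-level regression with a baseline covariate (4,000 trials, four classes per school assumed) gives 8.1-9.0% at CV 0.70.

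**4. Changing only the reference to t(28), CV 0.70.** The plain pooled sandwich still gives about 7-8%. Sandwich tests with two-level weights give 5.4-6.0%.

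**5. Small-sample methods, ICC 0.05, CV 0 / 0.4 / 0.70, no city term.**
- t-test on school means: 4.7 / 5.2 / 4.5%
- REML two-level with t(28): 4.7 / 5.4 / 4.9%
- CR2 sandwich with Satterthwaite df: 4.7 / 5.1 / 4.3%

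**6. City.** Assume three cities of 10 schools, exact 5:5 allocation in each, total ICC 0.05, and CV 0 to 0.70, with uncorrected methods throughout (20,000 trials per setting). If 20-40% of the between-school variance lies between cities and city is left out of the model, the rate is about 4-8%. If city is included, it is about 8-11%.

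**The case against.** **The plan does not name this test.** The sandwich is to be clustered on classroom, so the rates above apply only after a different correction. This stands. A reader might infer that 7-9% is the false-positive rate of the analysis as written; the documents do not support that. With classroom as the cluster the rate is about 15-28% under a school-level ICC of 0.025-0.05 and four classes per school (assumed). That belongs to the separate question of the cluster variable.

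**A condensed article may leave degrees of freedom and reference distribution to the analysis plan.** This stands for those details, and the normal reference is my assumption, not the article's statement. It does not answer the point, because the article does fix the estimator and the standard-error method. The downward bias of the plain sandwich remains with a t(28) reference.

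**The size is conditional.** This stands too. A reader might take 7-9% as a firm property of any school-level analysis. It is not: with equal schools the rate is 6-7%, the 8-9% needs the pooled estimator together with the CV of 0.70, and that CV is a planning value. Allocation within city with city omitted makes the test more conservative, possibly enough to bring it to 5% or below. But that would be two errors offsetting each other by an unknown amount, and including city with the uncorrected method makes the inflation worse.

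**The practical consequence is modest.** Agreed: it matters mainly for results close to 0.05.

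**Conclusion.** The concern holds in a conditional form. Section {20a} commits to a large-sample procedure that does not hold its 5% level with 15 schools per arm, and moving the cluster from classroom to school does not by itself give a 5% test.

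The range of 6-9% rests on a two-sided test, a normal reference, gamma school sizes and no difference between cities. The actual rate cannot be fixed from the documents, because they give neither the reference distribution nor the variation between cities. In the checks without a city effect, every uncorrected school-level version referred to the normal was above 5%, and every small-sample method was close to 5%. This is a moderate defect that should be corrected. It is smaller than the choice of classroom as the cluster, and best handled in the same edit.

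**What to change.** In the section on statistical methods for main outcomes {20a}, together with changing the cluster to school, replace the MLR and sandwich test by a small-sample method at school level that includes city. Either of these would do:

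- a REML model with a school random intercept and Kenward-Roger or Satterthwaite degrees of freedom; or
- a school-clustered CR2 sandwich with Satterthwaite degrees of freedom.

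Add a baseline-adjusted school-level t analysis as a check. State the reference distribution and that the test is two-sided. Between-school degrees of freedom start at 28, fall to 26 with two city terms (30 − 2 − 2), and fall further with each school-level covariate that {20a} allows. Replacing the normal by t(28) alone is not enough for the plain pooled sandwich.

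The cost is a change of wording, possibly other software for the primary model, slightly wider intervals, and stated power of about 90.5% instead of 92% under the plan's own formula (28 df, before any city terms).

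### Schools are randomised, but the main-outcome standard errors are clustered on classrooms with no school level, so between-school variance is left out and the type I error exceeds 5%

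*Protocol article*

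**What the plan says.** All references are to the protocol article.

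- **Randomisation.** Sequence generation {16a}: "The unit of randomization between groups is the schools and not the classes". Trial design {8} gives "30 schools in three cities (15 controls and 15 in the experimental group".
- **Sample size.** Section {14} works with 15 clusters per arm averaging 100 children, ICC 0.05 and a cluster-size CV of 0.70. With 15 schools per arm, those clusters are the schools.
- **Levels promised.** Outcomes {12}: "All outcomes will be measured at the individual level, but analyses will be multilevel based on schools and individuals".
- **Levels specified.** Statistical methods for main outcomes {20a} describes children nested in classrooms and computes the standard errors "using a sandwich estimator where the cluster variable will the classroom (i.e., teachers level". It then observes that "all the classrooms within the same school are receiving either Elos 2.0 or treatment as usual to avoid contamination among the teachers" and concludes: "Therefore, our analysis will be following a two-level approach". That section names no school random effect, school cluster variable or third level.

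**The concern.** Every class in a school is in the same arm, so the treatment contrast compares two sets of 15 schools. Its variance contains the between-school variance divided by the number of schools. A sandwich estimator clustered on the classroom treats classes of the same school as independent and drops the covariance between them.

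The reason given for stopping at two levels does not support the choice. Shared allocation within a school is exactly why the school has to be the cluster.

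Section {20a} applies this rule to all four TOCA analyses, and so to the primary observed-data intention-to-treat analysis named in section {20c}. Multiple imputation and CACE, the other analyses in {20c}, address missing data and adherence and do not address clustering. An ineffective programme would be declared effective more often than the stated 5%.

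**Working it through.** **Inputs from the protocol.** Difference 0.25, SD 0.80, ICC 0.05 (0.039 previously reported), 100 children per school, 15 schools per arm, CV 0.70, alpha 0.05 (taken as two-sided).

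**Assumed.** Four classes of 25 per school. Section {10} requires at least one class in each of four grades but fixes neither the number nor the size of classes. Any classroom ICC is also assumed.

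**Step 1: reproduce the stated power with schools as clusters.**
- L = 100×0.05 / (100×0.05 + 0.95) = 0.840
- Design effect = (1 + 99×0.05) / (1 − 0.49×0.840×0.160) = 5.95 / 0.934 = 6.37
- SE = 0.80 × √(2×6.37/1500) = 0.0737
- Power = Φ(0.25/0.0737 − 1.96) = 92.4%, against the stated 92%

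The sample size therefore treats the 0.05 as the ICC of the 100-child school.

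**Step 2: what each standard error contains.** Let s be the school ICC, c an additional classroom ICC, b the children per class and C the classes per school (equal sizes).
- Captured by the classroom sandwich: 1 + (b−1)(s+c)
- Full design effect: 1 + (b−1)(s+c) + b(C−1)s
- SE ratio = √(captured/full); type I error = 2×[1 − Φ(1.96 × SE ratio)]

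The missing term, b(C−1)s, is positive whenever there is any school variance and more than one class per school.

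**Step 3: results before baseline adjustment, four classes of 25.**

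| s | c | Captured | Full | SE ratio | Type I error |
|---|---|---|---|---|---|
| 0.05 | 0 | 2.20 | 5.95 | 0.61 | 23% |
| 0.05 | 0.05 | 3.40 | 7.15 | 0.69 | 18% |
| 0.05 | 0.10 | 4.60 | 8.35 | 0.74 | 15% |
| 0.025 | 0.025 | 2.20 | 4.075 | 0.73 | 15% |
| 0.01 | 0.04 | 2.20 | 2.95 | 0.86 | 9% |
| 0.005 | 0.045 | 2.20 | 2.575 | 0.92 | 7% |

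Simulation of the first row (2,000 null trials, 30 schools) gave 24%. At s = 0.039 and c = 0 the formula gives 22%. The planned 3800 children make about 127 per school (3800/30). Four classes of 32 then give 25% and eight classes of 16 give 34% (s = 0.05, c = 0).

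**Step 4: unequal school sizes.** At CV 0.70 with s = 0.05 and c = 0, unadjusted simulation gave 29% with four classes per school and 36% with classes of about 25.

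**Step 5: with the baseline outcome as a predictor, as {20a} specifies.** Simulation under assumed baseline-to-follow-up correlations gave:
- s = 0.05, c from 0 to 0.10, equal school sizes: about 11–24%
- the same at CV 0.70: about 11–31%
- 0.05 divided between school and classroom: about 7–13%

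For example, take equal sizes and a correlation of 0.6 for children and classes. With s = 0.05 and c = 0, the error is 18% if school effects correlate at 0.9 and 23% if they also correlate at 0.6.

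**Step 6: the same data analysed at school level.** In the unadjusted simulations a t-test on school means rejected in about 4–7% of null trials, mostly 4.5–5.5%. School-clustered standard errors with t on 28 df gave about 5–7% with equal sizes and 6–8% at CV 0.70.

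**The case against.** The strongest objection concerns size. A reader might infer that the false-positive rate is simply several times 5%. The document does not support that unconditionally, because it does not fix the inputs that set the multiple:

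- **Classes and ICC split.** Neither the number of classes per school nor the division of the ICC between school and classroom is given. Section {14} itself calls 0.05 conservative against 0.039. If most of the 0.05 belongs to the classroom, the excess is modest.
- **Baseline adjustment.** Section {20a} always includes the baseline outcome, and adjustment can remove part of the school variance. It does not do so reliably: when school effects are no more stable than child scores, the error stays at 23%.
- **Allocation within city.** Sections {16b} and {6b} allocate within each municipality. If 0.02 of the 0.05 lay between cities (assumed), the unadjusted simulated error falls from 24% to 17.5%.

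All three stand as reasons to report a range. None brings the error down to 5% in any setting examined.

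Two further inferences should be resisted. One is that the trial's design or its effect estimate is invalid. The sample size is sound on schools and its power reproduces. The choice of cluster affects standard errors, intervals and p-values, and does not bias the point estimate. The other is that the lack of a small-sample correction for 30 clusters is a separate error. The protocol proposes no school-clustered analysis to correct, and such detail is commonly left to the analysis plan. It matters only as part of the repair. Whether the named Mplus option is compatible with a model that has a within part is a software question that the document cannot settle.

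Section {12} might be read as already supplying the school level. It contradicts {20a} without repairing it, since {20a} is the operative text and names a different cluster. An unseen analysis plan might say otherwise, but the article states the wrong cluster explicitly.

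**Conclusion.** The concern holds. Section {20a} clusters below the unit of randomisation, on a rationale that points the other way, and conflicts with sections {12}, {14} and {16a}. The direction of the error is certain if there is any residual between-school variance: standard errors are too small and the type I error is above 5%.

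Its size is conditional. The 23% figure takes the protocol's 0.05 as the school ICC and assumes four equal classes of 25 with no adjustment. The adjusted ranges in step 5 are the fairer description of the planned analysis, and they also rest on assumed correlations and classroom ICCs. The figure closest to nominal, about 7%, requires most of the 0.05 to belong to the classroom.

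**What to change.** - In {20a}, name the school as the top-level cluster for all four main-outcome analyses. Either school-clustered standard errors or a model with a school random intercept and a classroom-within-school intercept will do. The second also represents the teacher as rater.
- State a small-sample reference suited to 30 schools, for example t on about 28 df. The choice among such methods is secondary.
- Remove the argument that shared allocation within schools justifies two levels, and make {12} and {20a} name the same levels.

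The cost is a change of analysis wording and model syntax, and wider but correct confidence intervals. The sample size already assumes school clusters, so its stated power is not undermined, and nothing changes in design or data collection.
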